## Abstract

**Background:**

Current psychological and pharmacological treatments for Anorexia Nervosa (AN) provide only moderate effective support, and there is an urgent need for research to improve therapies, especially in developing age. Non-invasive brain stimulation has suggested to have the potential to reducing AN symptomatology, via targeting brain alterations, such as hyperactivity of right prefrontal cortex (PFC). We suppose that transcranial direct current stimulation (tDCS) to the PFC may be effective in children and adolescents with AN.

**Methods:**

We will conduct a randomized, double blind, add-on, placebo-controlled trial to investigate the efficacy of tDCS treatment on clinical improvement. We will also investigate brain mechanisms and biomarkers changes acting in AN after tDCS treatment. Eighty children or adolescent with AN (age range 10–18 years) will undergo treatment-as-usual including psychiatric, nutritional and psychological support, plus tDCS treatment (active or sham) to PFC (F3 anode/F4 cathode), for six weeks, delivered three times a week. Psychological, neurophysiological and physiological measures will be collected at baseline and at the end of treatment. Participants will be followed-up one, three, six months and one year after the end of treatment. Psychological measures will include parent- and self-report questionnaires on AN symptomatology and other psychopathological symptoms. Neurophysiological measures will include transcranial magnetic stimulation (TMS) with electroencephalography and paired pulse TMS and repetitive TMS to investigate changes in PFC connectivity, reactivity and plasticity after treatment. Physiological measures will include changes in the functioning of the endogenous stress response system, body mass index (BMI) and nutritional state.

**Discussion:**

We expect that tDCS treatment to improve clinical outcome by reducing the symptoms of AN assessed as changes in Eating Disorder Risk composite score of the Eating Disorder Inventory-3. We also expect that at baseline there will be differences between the right and left hemisphere in some electrophysiological measures and that such differences will be reduced after tDCS treatment. Finally, we expect a reduction of endogenous stress response and an improvement in BMI and nutritional status after tDCS treatment. This project would provide scientific foundation for new treatment perspectives in AN in developmental age, as well as insight into brain mechanisms acting in AN and its recovery.

*Trial registration* The study was registered at ClinicalTrials.gov (ID: NCT05674266) and ethical approval for the study was granted by the local research ethics committee (process number 763_OPBG_2014).

## Introduction

### Background and rationale

Anorexia Nervosa (AN) is an Eating Disorder (ED) that involves significant biological, psychological, and social complications, typically associated with other severe physical and psychological comorbidities. Mortality and disability rates are high, and the incidence among children and adolescents is increasing [1, 2].

Treatment outcomes for AN remain modest with a high risk of relapse [3–5] and there is no specific Food and Drug Administration pharmacological indication for AN [6]. Although family-based or cognitive-behavioral therapy is widely considered the treatment of first choice [7], no single recommended psychological intervention has demonstrated clear superiority in treating adults or adolescents with AN [8, 9], so the effectiveness of multidisciplinary programs has been suggested [10]. Nevertheless, the development of new and more effective treatments for AN is highly claimed, especially in developmental age.

The emergence of neurobiological models of AN has opened the opportunity for brain-directed treatment approaches. Literature has reported brain abnormalities in AN, particulary in the dorsolateral prefrontal cortex (DLPFC) [11, 12], cingulate cortex and left middle occipital gyrus [13]. Studies of functional magnetic resonance imaging show wide variability. In the context of food cue, a hyperactivity in reward-related regions [14, 15] and a hyperactivity of right DLPFC [16] following exposure to palatable food cues have been reported, suggesting elevated top-down inhibition of reward processing [17–19]. Indeed, DLPFC plays a key role in cognitive control [20, 21], in self-control in a dietary context [22, 23] and in regulating the valence of emotional experiences [24].

Based on these studies, non-invasive brain stimulation techniques (NIBS), which may directly modulate neural circuits by enhancing or reducing the excitability of key brain regions, have been proposed as therapeutic option, for example to restore the balance between right and left DLPFC activity (for a recent review see [25, 26]). Several studies, using transcranial magnetic stimulation (TMS) and transcranial direct current stimulation (tDCS), have typically targeted the prefrontal cortex (PFC), mainly the DLPFC, with the aim of reducing the excessive top-down cognitive control of AN patients and have shown positive effects on AN symptomatology and related behaviors [25, 26].

Across NIBS techniques, tDCS refers to the application of weak direct currents (0.5–2.0 mA) to a specific region of the brain, transmitted through electrodes attached to the scalp [27]. tDCS can be used to elicit an excitatory (anodal) or inhibitory (cathodal) effect, depending on the polarity of stimulation, and may induce long term potentiation (LTP) like plasticity [28, 29]. Compared with TMS, tDCS produces minor transient side-effects and is well tolerated by children and adults, with almost no discomfort and no limitation of movement [30–33], it is also less expensive, technically less demanding, and easy to transport and use in different environments, including the home by patients under medical supervision [34]. Considering the advantages of using tDCS, especially in the pediatric population, evidence of tDCS treatment efficacy may lead to important changes in the treatment of AN, with a substantial reduction in the times and costs of interventions.

However, while larger evidence exists from studies conducted with TMS [35–37], a few studies have applied tDCS for the treatment of AN with promising results. Khedr et al. [38] reported an improvement of depressive symptoms in adult patients with AN following 10 daily sessions of anodal tDCS over the left DLPFC (anode F3/cathode extracephalic—over the contralateral arm). Similarly, Strumila et al. [39] showed a reduction in eating and depressive symptoms following 20 sessions of tDCS over DLPFC (anode F3/cathode F4). In addition, data from an open-label study of our lab on adolescents with AN showed a positive effect of 18 sessions of left anodal/right cathodal tDCS to PFC, resulting in stable weight gain and improvement of psychopathological symptoms superior to a psychological control treatment [40]. However, the generalizability of these findings is low due to the lack of a sham control group and small sample size.

Despite some promising results, the effectiveness of tDCS for the treatment of AN symptoms is not always consistent. Baumann et al. [41] did not observe effect of active tDCS over the left DLPFC (anode F3/cathode over the right orbitofrontal region Fp2) on psychopathology and weight recovery in adult patients with AN, in a sham-controlled study. However, a reduction of the need to follow specific dietary rules and an improvement of body image evaluation were showed in the active tDCS group.

Although accumulating evidence suggests the presence of alterations in cortical excitation-inhibition balance in some mental disorders, such as AN [42–44], a definitive neurobiological under pinning of AN is lacking and few studies have directly investigated the brain mechanisms acting in AN in developmental age. In recent years, the integrative approach combining TMS with electroencephalography (EEG) has demonstrated to be a valuable tool to non-invasively probe brain circuits, allowing assessment of several cortical properties such as connectivity, plasticity, cortical excitability and inhibition [45–47]. Compared with other available neurophysiological methods, TMS-EEG responses are more sensitive to brain state and are influenced by brain maturation and ageing [48, 49]. As such, TMS-EEG can be applied in both basic science and clinical research [50]. Applied to various clinical populations, this technique may offer the opportunity to identify pathological biomarkers in brain dynamics which may supply new early tool of diagnosis and the identification of innovative therapeutic targets [51], as well as biomarkers to monitor treatment effects [52].

In addition, specific physiological biomarkers also need to be further investigated in order to assess possible effects of tDCS treatment on the vulnerability to stressors. Indeed, alterations in the functioning of the hypothalamic–pituitary–adrenal (HPA) axis, the main component of the endogenous stress response system, have been consistently reported in patients with AN [53] and appear to normalize in patients with weight recovery [54].

Overall, to explore the neurobiological mechanisms acting in AN, the use of brain-based approaches has been promoted [25, 26, 55] and large-scale, high-reproducibility clinical trials investigating the neurophysiological features of AN and the specific brain changes induced by NIBS are urgently needed.

### Objectives

We hypothesized that excitatory tDCS over the left PFC and inhibitory tDCS over the right PFC (anode left/cathode right) may aid in altering/resetting inter-hemispheric balance in children and adolescents with AN, reducing their control over eating behaviors and improving the AN psychopathology, assessed as changes in Eating Disorder Risk composite score (EDRC) of the Eating Disorder Inventory (EDI-3) as primary outcome. The study also aims to investigate some neurophysiological mechanisms that characterize AN, as well as the association between efficacy and neurophysiological effect of tDCS treatment and physiological response to treatment, as secondary outcome. We will employ TMS-EEG to directly explore inter-hemispheric balance in the DLPFC activity of children and adolescent with AN. Moreover, paired pulse TMS (pp-TMS) and repetitive TMS (rTMS) protocols will be used to investigate the functional mechanisms within the PFC of youth patients with AN. We hypothesized that at baseline there are differences between the right and left hemisphere in some electrophysiological measures such as inhibitory/excitatory motor circuits, sensory-motor integration, cortical plasticity, cortical oscillations, reactivity, and functional connectivity, and that such differences will be reduced after tDCS treatment. In addition, an increase in cortical plasticity after tDCS treatment is expected. Finally, we will assess if potential changes of specific biomarkers, such as those related to the endogenous stress response system functioning, nutritional status and body mass index (BMI), will occur after tDCS treatment and correlate with clinical improvement. Specifically, we hypothesized a reduction of endogenous stress response and an improvement of nutritional status and BMI after tDCS treatment.

In particular, this project has three different specific aims:*Specific Aim 1 “clinical efficacy”*: To evaluate the clinical efficacy of anodal/right cathodal tDCS to the PFC, coupled with a treatment-as-usual (TAU), in children and adolescents with AN in terms of: (1) changes in psychopathological measures, specifically changes in EDI-3 ED-specific (EDRC score) as primary outcome and changes in other psychopathological measures as secondary outcome; (2) changes in physiological measures, such as endogenous stress response system functioning, nutritional status, and BMI, as secondary outcome; (3) long-lasting effects until one year follow-up.*Specific Aim 2 “neurophysiological characterization at baseline”*: To characterize at baseline AN patients in terms of (1) intra-cortical inhibitory/excitatory motor circuits, and sensory-motor integration using pp-TMS; (2) cortical plasticity using rTMS; (3) cortical oscillations, reactivity, functional connectivity using TMS-EEG co-registration and to assess interhemispheric dynamics in terms of balance and inhibition.*Specific Aim 3 “association between efficacy and neurophysiological effect of tDCS treatment”*: To determine the neurophysiological patterns associated to behavioral changes induced by tDCS treatment, we will evaluate changes on plasticity and connectivity of the prefronto-motor networks, assessed by TMS-EEG, pp-TMS and rTMS, and their association to improvement.

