#### Secondary outcome measures

Secondary psychological outcome measures will be collected at T1, T2, T3, T4 and T5, physiological outcome will be collected at T1, T2 and T4 and only BMI also at T3 and T5, instead neurophysiological outcome measures will be collected only at T1.

Improvement on the other EDI-3 composite scores, EAT-26 total score, BUT-GSI, and CBCL 6–18, YSR 11–18, MASC-2 and CDI-2 subscale’s t-scores, will be considered as secondary psychological end-points.

Possible reduction of left and right hemisphere baseline differences in TEPs, in SICI/ICF and SAI protocols, and increase MEP amplitude in iTBS protocol will be considered as neurophysiological secondary end-points.

Finally, reduction in the CAR, CAR AUCg and AUCi and improvement in nutritional state and BMI, which have normative data for age and sex, will be adopted as secondary physiological end-points.

See Table 1 for details on the outcome measures.

**Table 1. Tab1:** Outcome measures.

Primary outcome measure	Secondary outcome measures	
EDRC score (EDI-3)	Psychopatological	IC, IPC, APC, OC, GPMC scores (EDI-3) EAT-26 total score BUT-GSI CBCL 6–18 subscale’s t-scores YSR 11–18 subscale’s t-scores MASC-2 subscale’s t-scores CDI-2 subscale’s t-scores
	Neuropsysiological	TEPs, SICI/ICF and SAI protocols MEP amplitude in iTBS protocol
	Physiological	CAR, CAR AUCg and AUCi Nutritional state and BMI

*APC* Affective problems, *BMI* Body Mass Index, *BUT* Body Uneasiness Test, *CBCL 6–18* Child behavior checklist for ages 6–18, *CDI-2* Children’s depression inventory—second edition, *AUCg* Cortisol area under the curve relative to the ground, *AUCi* Cortisol area under the curve with respect to the increase, *CAR* Cortisol awakening response, *EAT-26* Eating Attitudes Test, *EDI-3* Eating Disorder Inventory, *EDRC* Eating Disorder Risk, *GPMC* General Psychological Maladjustment, *GSI* global severity index, *IC* Ineffectiveness, *IPC* Interpersonal problems, *MEPs* Motor-Evoked Potentials, *MASC-2* Multidimensional Anxiety Scale For Children—second edition, *OC* Overcontrol, *SICI/ICF* Short intracortical inhibition and facilitation, *SAI* Short-latency afferent inhibition, *iTBS* Theta burst stimulation, *TEPs* TMS-evoked potentials, *YSR 11–18* Youth Self-Report for Ages 11–18.

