### Statistical methods

The Shapiro–Wilk test will be used to test the normality of the data and Levene’s test for the homogeneity of variances. When data will be normally distributed and the assumption of homogeneity will be not violated, parametric analyses will be computed. When one assumption will be not meet, non-parametric tests will be conducted or a log-transformation of distribution will be applied, if appropriate.

The groups will be compared on demographic and categorical variables using Chi-Square analyses. The primary outcome (EDRC score of EDI-3) will be included in a General Linear Model and will be analyzed by means of repeated measures ANOVA with Group (active tDCS + TAU vs sham tDCS + TAU) as between-factor and Follow-ups (T0-T1 vs T0-T2 vs T0-T3 vs T0-T4 vs T0-T5) as within-factor. The same analyses will be applied to the secondary psychological outcomes (EAT-26 total score, BUT-GSI, and CBCL 6–18, YSR 11–18, MASC-2 and CDI-2 subscale’s t-scores). Post hoc comparisons will be run by means of Bonferroni test.

For secondary neurophysiological outcomes, the differences between the left and right hemisphere at baseline and between the recordings T0 and T1 will be evaluated on both TEPs component and frequency through a non-parametric cluster based permutation tests to correct for multiple comparisons as developed in the ft_timelockstatistics\ ft_freqstatistics functions in Fieldtrip [74]. The EEG signal will be analyzed for defining a resting state pattern with frequency inspection, using a Fourier analysis. For TMS data, prior to undergoing ANOVA, the normal distribution of data will be assessed by means of the Shapiro-Wilks test. The level of significance was set at 0.05. For the SICI, SAI, and iTBS protocols, we will perform three ANOVAs on the normalized values calculated as the percentage of the mean peak-to-peak amplitude size of the unconditioned TS with GROUP (active vs sham) as the between-subject factor and ISI (for SICI and SAI protocols) or TIME (for iTBS protocol) as within-subject factors. When a significant main effect will be reached, Bonferroni post hoc comparisons will be performed to characterize the specific effect.

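### Reduction of left-right hemispheric differences after tDCS is a secondary end-point, but no analysis in Statistical methods tests it against sham

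*Protocol article*

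**What the plan says.** All references are to the protocol article.

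- **Objectives.** The baseline hypothesis is that "at baseline there are differences between the right and left hemisphere in some electrophysiological measures". The candidate domains are "inhibitory/excitatory motor circuits, sensory-motor integration, cortical plasticity, cortical oscillations, reactivity, and functional connectivity", and the sentence goes on "and that such differences will be reduced after tDCS treatment". The Discussion part of the Abstract repeats the expectation: "such differences will be reduced after tDCS treatment".
- **Secondary outcome measures.** The neurophysiological end-points include "Possible reduction of left and right hemisphere baseline differences in TEPs, in SICI/ICF and SAI protocols". For iTBS the end-point is a rise in MEP amplitude, not a change in asymmetry.
- **Statistical methods, TEPs and frequency.** The plan is that "the differences between the left and right hemisphere at baseline and between the recordings T0 and T1 will be evaluated on both TEPs component and" (the quote is cut here; the other domain follows), by "non-parametric cluster based permutation tests to correct for multiple comparisons". No active-versus-sham term is given.
- **Statistical methods, TMS protocols.** There are three ANOVAs, for SICI, SAI and iTBS, "with GROUP (active vs sham) as the between-subject factor and ISI (for SICI and SAI protocols) or TIME (for iTBS protocol) as within-subject factors".
- **Neurophysiological measures.** Recordings are made at T0 and T1 only, with each hemisphere in its own session. TMS-EEG stimulates M1 and DLPFC on each side.

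**The concern.** The end-point has three ingredients: hemisphere (the left-right difference), visit (T0 to T1) and, since it is meant to follow from tDCS, treatment arm. Each planned analysis leaves out at least one of them. If the plan is followed as written, the trial can report that asymmetry fell between T0 and T1 without having asked whether it fell more under active stimulation than under sham.

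All patients receive usual treatment for six weeks, and a group difference that is partly chance at T0 tends to be smaller at T1. Either could be taken for a tDCS effect. The stakes are the trial's account of mechanism: the main Discussion section intends these recordings as a neurophysiological marker of response.

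**Working it through.** **1. The end-point set against the planned tests**

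| Analysis in Statistical methods | Hemisphere | Visit (T0/T1) | Active vs sham |
|---|---|---|---|
| TEP/frequency, first contrast | yes | no, T0 only | no |
| TEP/frequency, second contrast | not stated | yes | no |
| SICI and SAI ANOVAs | no | no | yes |
| iTBS ANOVA | no | not stated | yes |

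No row has all three. TIME in the iTBS model most naturally means the recording times after stimulation, which the TMS protocols section describes. Even if it meant visit, iTBS is not among the asymmetry end-points. In the same section the cortisol and BMI analyses do name both group and visit.

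**2. The plan's only figure**

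Sample size concerns EDRC, with f = 0.08, correlation 0.80, 2 groups and 6 measurements. For the within-between interaction at N = 68:

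- λ = f²·N·m/(1 − ρ) = 0.0064 × 68 × 6 / 0.20 = 13.06, with 5 and 330 degrees of freedom
- power 0.8004
- 68/0.85 = 80

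The figure reproduces, but it does not cover the hemispheric end-points.

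**3. What a T0-T1 test without a group term would show under the null**

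Assume no true asymmetry and no change at all. Let Z0 and Z1 be the standardised mean left-right differences at T0 and T1, with correlation r. The documents give no r for these measures, so a range is used. The reduction statistic is (Z0 − Z1)/√(2(1 − r)), and its correlation with Z0 is √((1 − r)/2).

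Without selection on Z0, the one-direction false-positive rate is 2.5%. Given a significant T0 difference, the mean difference at T1 is r times its T0 size, and:

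| r | √((1 − r)/2) | P(significant reduction, given significant T0) |
|---|---|---|
| 0.3 | 0.592 | 24.3% |
| 0.5 | 0.500 | 18.5% |
| 0.7 | 0.387 | 12.9% |
| 0.8 | 0.316 | 10.1% |
| 0.9 | 0.224 | 7.1% |

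A patient-level simulation (n = 80) agrees: 25.1%, 18.9%, 13.1% and 7.3% at r = 0.3, 0.5, 0.7 and 0.9. Testing T0-T1 in the active arm alone (40 patients), after selection on all 80, gives 13.6%, 11.8%, 8.5% and 5.6%. Splitting by arm without comparing the arms therefore does not remove the bias.

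**4. The same measure compared between arms**

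With equal arms, the difference in change between active and sham is uncorrelated with the pooled T0 mean. Selection on that mean therefore leaves the rate at 2.5%. The simulation gave 2.6%, 3.0%, 2.2% and 3.0% at the same four values of r.

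**5. How often the whole sequence occurs**

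The percentages in step 3 are conditional. At r = 0.5, a false T0 difference followed by a significant reduction has probability 0.05 × 0.185 = 0.9% per measure. An upper bound is 4 × 0.9% ≈ 3.7% over four tests and 7.4% over eight. Over r = 0.8 to 0.3 the bounds are about 2% to 5% and 4% to 10%.

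**6. Reach of the cluster correction**

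Cluster permutation controls error over channels and time or frequency points inside one test, not across tests. The article does not state how many tests there are. Assume two areas by TEP and frequency (4 tests), or with theta, alpha and beta tested separately (2 × 4 = 8). The chance of at least one false baseline asymmetry is then 1 − 0.95⁴ = 18.5% or 1 − 0.95⁸ = 33.7% if the tests are independent. At an assumed between-test correlation of 0.5 it is 15.5% or 25%, and at 0.8 it is 11% or 16%.

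**The case against.** **Selection is not a written rule.** A reader might infer that the plan picks measures because their T0 difference was significant, so that chance asymmetries are bound to be reported as corrected by tDCS. The documents do not say this. Secondary outcome measures fixes the measures in advance with no condition on T0, and Statistical methods lists the two contrasts side by side. The wording in Objectives permits selection but does not require it. This stands: the figures in step 3 hold only under that reading, and the joint event is far rarer.

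**The trial has a sham arm.** Sham patients would show the same regression to the mean, and GROUP is in three ANOVAs. This is true of the design, but the protection works only if the asymmetry change is compared between arms, and no listed analysis does that.

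**These are secondary, exploratory measures, and an analysis plan may fill the gap.** The text speaks of exploring and characterising. A deciding contrast and a multiplicity rule for such measures are commonly left to a fuller plan. A reader might also infer that one chance difference would let Aim 2 be declared confirmed, but the article sets no such success rule. This part stands, so the lack of a single deciding contrast is not the point here. What remains is that the article does set out its tests and their factors, and as listed they do not address the end-point it declares.

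**The multiplicity statement is not false.** The article never claims that the cluster correction reaches across areas or measures. Agreed. A clarifying sentence is enough.

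**Conclusion.** The point holds in this form: an asymmetry-reduction end-point is declared, and none of the listed analyses compares it between active and sham. That follows from the text and needs no assumption. A T0-T1 reduction found by the listed tests could not be attributed to tDCS rather than to usual treatment, time or regression to the mean.

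The size of the regression part does rest on assumptions. It requires that attention falls on measures significant at T0, and it depends on an unstated T0-T1 correlation: 10% to 24% for r = 0.8 to 0.3, about 7% at r = 0.9, against 2.5% nominal. Unconditionally it is about 0.9% per measure at r = 0.5. Change under usual treatment or over time would bias the attribution without any selection, and the documents give no basis for sizing it.

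A fuller plan that is not shown may contain the missing contrast. The EDRC analysis and the sample size are not affected.

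**What to change.** In Statistical methods:

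1. For each asymmetry end-point measure (TEPs, SICI/ICF, SAI), define the left-right difference at T0 and at T1.
2. Compare its T0-T1 change between active and sham (group × visit × hemisphere). For TEPs and frequency this can be a cluster permutation test of the between-arm difference in change.
3. Include all patients with recordings, whether or not the T0 difference was significant.
4. State that the cluster correction applies within each test only, and report baseline left-right results across areas, bands and protocols as exploratory.

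The cost is wording, with no extra patients, visits or recordings. The between-arm contrast is less precise. With s the SD of individual change and 80 patients in equal arms, its standard error is s·√(1/40 + 1/40) = 0.224s, against s/√80 = 0.112s for the pooled mean change, so power is lower for change that occurs in both arms. If only the active arm changes, by δ, the pooled mean is δ/2 and the two ratios of effect to standard error are equal. The power given up is thus for change shared with sham, which is not a tDCS effect.
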